### Quality control

2.11

To ensure trial quality, the quality supervisor will verify all the process details and check the authenticity of the data at regular intervals. Since differences among centers can cause bias, the evaluation of the scales in each sub centers will be performed by 2 psychiatrists who have undergone the same evaluation criteria to reduce the bias. To record the attendance and compliance, we make record cards for patients which cover date of treatment, personal information, and their signatures after every treatment.

## Discussion

3

Ischemic stroke is a major chronic non-infectious disease that seriously endangers health, which is the main cause of persistent and acquired disability in adults worldwide.^[3,24]^ Numerous clinical studies and practices have shown that acupuncture is effective for stroke and less adverse reactions.^[25,26]^ However, the current studies mainly focus on the observation of the efficacy, the mechanism of acupuncture treatment for ischemic stroke has not been concluded. Therefore, we hope to obtain high-quality research data from this multicenter clinical trial, so as to provide reliable basis for future related studies.

Acupuncture manipulation is an important link in the process of acupuncture treatment and one of the key factors affecting the curative effect. As one of the basic acupuncture techniques, twisting manipulation is widely used in clinical. A large number of theoretical, basic and clinical studies have shown that different acupuncture stimulation have different effects.^[27,28]^ Using different twist stimulation, the treatment effect of the same disease is different, using the same twist stimulation in the treatment of different diseases, the therapeutic effect is not the same.^[29,30]^ This study can determine which time or frequency is most important in the course of acupuncture treatment for ischemic stroke. Whether there are differences in cerebral functional connections over time and frequency. The optimal combination of stimulation time and frequency can be obtained by observing the changes of cerebral functional connections through orthogonal trial design.

The purpose of this study was to evaluate the central mechanism of acupuncture stimulation quantity using time and frequency as control conditions. Our study protocol was designed through extensive discussion of several previous relevant studies.^[31–33]^ We try to minimize any biases that might affect the results of the study. By observing the changes of cerebral functional connectivity based on fMRI, this study will provide reasonable stimulation parameters and strong mechanism evidence of cerebral central network for the use of acupuncture for ischemic stroke.

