**Conclusion::**

The purpose of this study was to evaluate the central mechanism of acupuncture stimulation quantity using time and frequency as control conditions. This study will provide reasonable stimulation parameters and strong mechanism evidence of cerebral central network for the use of acupuncture for ischemic stroke.

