### Study design

2.1

This is a multicenter, central-randomized, controlled, double-blind, noninferiority, 2 factors and 3 levels orthogonal trial. A total of 100 participants were randomized into experimental group and control group, the experimental group was divided into 9 groups (A1-A9) according to different factors or levels, and each group have 10 participants. This trial recruited participants from 3 sub centers: the First Affiliated Hospital of Yunnan University of Traditional Chinese Medicine (TCM), the Affiliated Hospital of Yunnan University and Kunming Yan’an Hospital, recruitment advertisements will be placed on the network and bulletin boards. Eligible participants will have an equal chance of being allocated randomly to experimental group or control group.

The whole study period is 17 days, including 1 week for baseline observation, 3 days treatment and observation, and 1 week follow-up. Participants will be monitored cerebral functional connectivity changes by fMRI before and the 0 hour, 24 hours, 36 hours after treatment, and scales was used to evaluate the clinical efficacy during the treatment and follow-up period. Figure 1 shows a flowchart of the study.

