### Randomization, allocation concealment, and blinding

2.6

After recruitment, a statistician who is not taking part in the clinical intervention will use SPSS 25.0 (IBM, Chicago, IL) to generate a random allocation sequence, the eligible participants who meet the inclusion criteria will be randomly distributed to experimental group and control group with proportion of 9:1. Participants in the experimental group will random reassignment to A1-A9 via the central randomization system by statistician from each sub centers. Each subject will received a unique random ID. The allocation concealment procedure will not be exposed until the clinical trial is finished completely. The baseline assessment and questionnaire administration was conducted by researcher A. Assessments and measurements of the participants will be carried out before and after the treatments by researcher B. Researcher C as image analyst will processed and analyzed the fMRI images to observed the cerebral functional connectivity changes. A licensed acupuncture researcher who has worked for more than 10 years will conduct acupuncture intervention on participants, whereas all subjects will deprived from knowing something about the pattern of treatment.

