#### Experimental group

2.7.1

The acupoint prescription was “Shenyang Tongdu” acupuncture according to TCM theory and clinical experience. Acupoints are including DU14 (Dazhui), DU9 (Zhiyang) and DU4 (Mingmen). The experimental group adopted 2 factors and 3 levels orthogonal trial, the 2 factors of time and frequency include 3 levels of different parameters, and the intersection of different parameters constituted 9 groups (A1-A9). Time refers to the operating time, including 60 seconds, 120 seconds, 180 seconds. Frequency refers to the twists per minute without lifting, including 120 bpm, 180 bpm, 240 bpm, the range of twirling manipulations is about 180°. Participants only received acupuncture once, and the rest of the time was observation and follow-up period. Specific parameters of each experimental group are shown in Figure 2.

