### Statistical analysis

2.10

The BOLD-fMRI data processing and analysis is based on the DPABI 4.3 of Matalab platform. Including removal of the first 10 time points, time correction, head movement correction (eliminating the data of head movement translation >2 mm or rotation shift >2°). Regression white matter and cerebrospinal fluid signals were used to remove interference. Spatial normalization, spatial smoothing, and linear drift removal were performed. If the data met normal distribution, the image characteristics of the postacupuncture effect were investigated by paired T-test.

Firstly, a gray matter mask was made for the subjects in this study, and the differences before acupuncture were found by paired T-test (*P* < .05). The whole brain gray matter mask was used to subtract the areas with significant differences before acupuncture, so as to exclude the pixels with significant differences at baseline. Paired T-test was used to investigate the changes of fALFF, ReHo, DC, and seed point FC before and after acupuncture in the intra-group comparison. Paired T-test was used to further find the differences in cerebral activity between groups compared with different stimulation quantity. The statistical results were corrected, if the threshold voxel level *P* < .01 and the cluster level *P* < .05, the difference was statistical significance.

Continuous outcome variables including NIHSS scores, MBI scores, Brunnstrom scores and stroke Chinese medicine symptom scores at before and the 0 hour, 24 hours, 36 hours after treatment, and 1 week follow-up will be analyzed with univariate repetitive measurement deviation analysis. Chi-Squared test will be used for comparison between groups.

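### The Discussion promises an optimal time-frequency combination and a ranking of the two factors, but the stated fMRI analysis contains no test that could deliver either

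*Protocol article*

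**What the plan says.** The design has 100 participants. In Study design, "the experimental group was divided into 9 groups (A1-A9) according to different factors or levels, and each group have 10 participants". Patients are "randomly distributed to experimental group and control group with proportion of 9:1". Under Experimental group, A1-A9 are the full crossing of operating time (60, 120, 180 seconds) with twisting frequency (120, 180, 240 per minute).

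The Discussion makes two firm statements about what this layout will yield: "This study can determine which time or frequency is most important in the course of acupuncture treatment for ischemic stroke" and "The optimal combination of stimulation time and frequency can be obtained by observing the changes of cerebral functional connections through orthogonal trial design". The Abstract's Conclusion is softer but still unconditional: "This study will provide reasonable stimulation parameters and strong mechanism evidence of cerebral central network".

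For the imaging outcome, Statistical analysis names paired t-tests before and after acupuncture within groups, and then: "Paired T-test was used to further find the differences in cerebral activity between groups compared with different stimulation quantity". Results are described as corrected, with thresholds of P < .01 at voxel level and P < .05 at cluster level. Four measures are analysed (fALFF, ReHo, DC and seed-point FC), and Primary outcomes lists scans before treatment and at 0, 24 and 36 hours after it.

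**The concern.** Deciding which of two crossed factors matters more, and which of nine combinations is best, are factorial questions. They call for estimates of the time effect, the frequency effect and their interaction, and for contrasts among the nine cells with error control. A set of pairwise group comparisons gives neither. A significant pair shows that two cells differ somewhere in the brain. It does not show that one cell is best of nine, and it does not compare the two factors.

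Nor does the article link its significance threshold to the choice of optimum or to the ranking of factors. The promise therefore goes further than the analysis. At stake is a published recommendation on stimulation parameters that chance alone could produce, with an apparent advantage inflated by selection.

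**Working it through.** **Sample size.** 9 x 10 + 10 = 100, and 9:1 allocation gives 90/9 = 10 per experimental cell and 10 controls. The plan's total is reproduced. The article states no effect size, SD or error rate for choosing an optimum.

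**Assumptions for the rest.** One normally distributed change score per patient, SD 1, nine cells of 10, one measure at one time. The real analysis is voxel-wise, so the results illustrate scale only. Simulated figures use 40,000 trials unless stated otherwise.

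**(a) Optimum chosen by ranking, no true effect.**
- The SE of a cell mean is 1/√10 = 0.316.
- The expected maximum of nine standard normals is 1.485. The top cell therefore lies 1.485 x 0.316 = 0.47 SD above its true mean on average.
- By symmetry the best-minus-worst gap averages 2 x 0.47 = 0.94 SD (simulation: 0.94).
- Each cell is the winner in about 1/9 = 11% of trials.
- Time has the wider range of level means in 50% of trials.
- An unadjusted two-sample t-test of best against worst (18 df) gives P < .05 in 50% of trials (100,000 draws).

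**(b) Optimum chosen through pairwise tests, no true effect.**
- Number of pairs among nine cells: 9 x 8/2 = 36.
- With each pair at 5% and no correction across pairs, at least one is significant in 57% of trials (two-sample t). With the paired t as written, pairing patients of different groups arbitrarily, the figure is 63%.
- Independent tests would give 1 - 0.95^36 = 84%, but the pairs share cells, so the simulated figures are the relevant ones.
- Four measures at three post-treatment times give 4 x 3 = 12 such families, so the chance over all of them is higher.

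**(c) Claim made only after a factorial test, no true effect, one measure at one time.**
- Overall F-test (8 and 81 df): 5%.
- Either main effect at 5% each: 10%.
- Either main effect or the interaction at 5% each: 14%, which is why these tests need joint control.

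**(d) What 10 per cell can support.** Suppose one cell exceeds the other eight by d. The noncentrality of the overall F-test is 10 x d² x 8/9, and the critical value is 2.05.

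| d (SD) | Noncentrality | Power of overall F-test | True best cell has the largest mean |
|---|---|---|---|
| 0.2 | 0.36 | 6% | 25% |
| 0.5 | 2.22 | 13% | 56% |
| 0.8 | 5.69 | 31% | 83% |

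Even a true advantage of half an SD is missed by the ranking in 44% of trials and by the overall test in 87%.

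**The case against.** A reader might infer that the plan contains a selection rule that names a winner with certainty and has no false-positive control. The article does not support that. It nowhere states a largest-mean pick or a range analysis. Its between-group comparison has a voxel and cluster threshold that can come out null. The Discussion itself leaves the matter open: "Whether there are differences in cerebral functional connections over time and frequency". A gated reading is therefore possible, and the certainty of a winner belongs only to an assumed ungated ranking.

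A reader might also take the optimum to be the trial's main conclusion. The Introduction gives the primary objective as the central network mechanism, and stimulation parameters are one of two deliverables.

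It can further be said that an article may leave the derivation of the optimum to the full protocol or SAP, and that one scalar score does not describe voxel maps. Both are fair. The missing derivation is not the point, and the figures are illustrative.

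What remains is that the promises are in the text without condition, and that the analysis in the same text is of a kind that cannot deliver them. The threshold does not close the gap: it is not tied to either claim, and the article does not say that its correction reaches across the 36 pairs, four measures or three times.

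**Conclusion.** The point holds as a mismatch between a stated promise and a stated analysis. The Discussion, and more softly the Abstract, commit the trial to a dominant factor and an optimal combination. The imaging analysis consists of pairwise paired t-tests, which can establish neither.

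The size depends on how the optimum would be chosen, which the article does not say. For one scalar measure at one time with no true effect, the chance of a basis for naming a winner runs from about 5% (gated by an overall F-test), through about 57% (any of 36 uncorrected pairs), to 100% (pure ranking). In the last case the apparent advantage of the top cell averages about 0.47 SD. These figures rest on normality, SD 1 and 10 complete patients per cell. The claims should be made conditional before results are seen; the design itself need not change for this.

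**What to change.** 1. Analyse each patient's fMRI change in A1-A9 with a between-subject 3x3 model containing time, frequency and their interaction, in place of paired t-tests between groups. Control multiplicity across these three tests and across measures and scan times.
2. Name an optimal combination or a dominant factor only if the relevant tests and multiplicity-adjusted contrasts support it. Otherwise report that no optimum was identified, with simultaneous confidence intervals for the cells.
3. In the Discussion and Abstract, replace the wording that the trial can determine, can obtain or will provide these results with wording that it will explore them.

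The cost is analysis work and less definite conclusions. With 10 per cell the trial will seldom name a single optimum: the overall F-test has about 13% or 31% power if one cell is better by 0.5 or 0.8 SD. A stricter rule requiring the best cell to be separated from all eight others (Hsu's multiple comparisons with the best, family-wise 5%) would name a truly best cell alone in less than 1% or about 2.6% of trials at those effects. It is therefore not recommended as the only route to a conclusion.
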